## Abstract

**Background::**

The neurogenic bowel dysfunction is a kind of familiar sequelae of the spinal cord injury (SCI), occurring in 70 to 80 percent of the SCI patients. The nursing intervention based on quantitative evaluation is to fully consider and assess the disease condition of patients, implement the personalized programs of nursing intervention, meet the patient's nursing needs to the maximum extent, improve the quality of nursing, and then facilitate the rehabilitation of patients. Our aim is to implement this program to evaluate the impact of this nursing intervention based on quantitative evaluation on the quality of life and bowel function in the neurogenic bowel dysfunction patients after SCI.

**Methods::**

The experiment is a randomized clinical research which will be implemented from May 2021 to October 2021 at the First Affiliated Hospital of Soochow University. The experiment was granted through the Research Ethics Committee of the First Affiliated Hospital of Soochow University (No.100238765). Fifty neurogenic bowel dysfunction patients after SCI confirmed via the imaging are included in this study. The patients with the history of bowel diseases or patients who are unwilling to cooperate with the evaluation will be excluded. The primary outcomes are bowel function recovery and satisfaction of the patients. The secondary outcomes are quality of life evaluated by SF-36 questionnaire. The questionnaire involves physical pain, role physiology, physiological functions, social functions, vitality, general health, mental health and role-motional.

**Results::**

Comparison of clinical parameters between the 2 groups will be shown in Table 1.

**Conclusion::**

Nursing intervention based on the quantitative evaluation can improve the quality of life and recovery of intestinal function for the neurogenic intestinal dysfunction patients after SCI.

**Trial registration number::**

researchregistry6143

## Introduction

1

The neurogenic bowel dysfunction is a kind of familiar sequelae of the spinal cord injury (SCI), occurring in 70% to 80% of the SCI patients.^[1,2]^ For patients with SCI, this is a significant problem, which will cause adverse effects on mental, social and physical health.^[3–5]^ When patients with SCI are asked to list the adverse effects on their quality of life in order of importance, intestinal dysfunction ranked second. Intestinal dysfunction secondary to SCI can cause urinary incontinence, uncoordinated defecation and constipation.^[6,7]^ The degree of dysfunction may be influenced via the external factors or the internal features of SCI itself, and may cause social or personal economic burden.^[8,9]^ Therefore, the attention should be focused on identifying the effective interventions to improve the intestinal function.

Generally, the treatment of intestinal function has attracted more and more attention, despite the relevant research is still very few in this field. In recent years, nursing intervention has increasing influence on the quality of life and intestinal function in the neurogenic bowel dysfunction patients.^[10]^ The traditional nursing approaches are conformist, focusing only on the basic nursing and treatment of the diseases, ignoring the effect of this disease on the quality of treatment and nursing. Hence, traditional nursing has been unable to meet the psychological and physiological needs of patients. The former investigations have indicated that the nursing intervention based on quantitative evaluation is to fully consider and assess the disease condition of patients, implement the personalized programs of nursing intervention, meet the patient's nursing needs to the maximum extent, improve the quality of nursing, and then facilitate the rehabilitation of patients.^[11]^ However, no reliable evidence has been reached due to the poor study design. Our aim is to implement this program to evaluate the impact of this nursing intervention based on quantitative evaluation on the quality of life and bowel function in the neurogenic bowel dysfunction patients after SCI.

## Materials and methods

2

The experiment is a randomized clinical research which will be implemented from May 2021 to October 2021 at the First Affiliated Hospital of Soochow University, in accordance with the purposes of the Declaration of Helsinki. The experiment was granted through the Research Ethics Committee of the First Affiliated Hospital of Soochow University (No.100238765) and recorded in research registry (researchregistry 6143). The recruited patients are given the written informed consent before registration. Fifty neurogenic bowel dysfunction patients after SCI confirmed via the imaging are included in this study. The patients with the history of bowel diseases or patients who are unwilling to cooperate with the evaluation will be excluded. Via utilizing the number table, all the patients involved in the experiment are assigned a random number in a random envelope, and the allocation results are hidden from them. The patients are randomly divided into control group (25 cases) and study group (25 cases).

### Nursing in both groups

2.1

In control group, the patients are given the routine nursing, containing psychological nursing and the education of disease health. The patients are guided to eat more foods with high dietary fiber, fresh fruits and vegetables, drink more water, facilitate intestinal patency, and eat less candies and milk that are prone to gas production, so as to decrease abdominal distension.

Nursing in study group involves:

(1)Quantitative evaluation: on the basis of the imaging examination results and clinical symptoms, the patients are scored in severe, moderate and mild.(2)Individualized nursing intervention:a.Reduce the intake of high-protein and high-fat food. If conditions permit, the daily intake of liquid should be at least 2000 ml.b.Implement an abdominal massage to speed up defecation. While massaging, patients are in the supine position. Centering on the navel, the nurse utilizes one or both hands’ fingers to circle the anatomical position of the colon from right to left, lasting for twenty minutes.c.Exercise muscles involved in the defecation: guide the patients to exercise their abdominal muscles. The patient is in the bed slope position or sitting on the toilet. Abdominal muscles are trained via abdominal breathing, deep breathing as well as defecation. Instruct the patient to perform the anal contraction exercises correctly. The patients’ knees slightly flexed apart with legs together and is in a supine position. Subsequently, patients raise buttocks and then contracts anus as instructed. In the process of anus contraction, the thigh muscle and perineal muscle contract for 6 seconds and relax for 4 seconds.d.Stimulate anus, facilitate colorectal reflection: the action of anal can stimulate intestinal peristalsis. The nurse put on gloves, lubricate middle finger and index finger with the liquid paraffin, inserts into anus slowly and then rotates in rectum. Anal action is implemented daily for 2 minutes.

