## Discussion

4

The bowel dysfunction is one of the most familiar problems in the patients with SCI.^[13,14]^ In the early injury stage, the anal sphincter and rectum internal layer are in the stage of total incontinence. After the acute phase, the voiding reflex recovers with the recovery of the lumbosacral central spinal cord.^[15]^ The right side of colon and the bowel are peristalsis supplied by the vagal innervation, so that the feces can be transported to large intestine. After the SCI, patients may have several problems, for instance, reduced sensation and muscle strength, and impaired respiratory as well as other functions.^[16]^ Specifically, SCI can lead to the high spasticity and paralysis of anal sphincter, or lead to the voiding dysfunction. The participation of pelvic and abdominal muscles and effective movement of bowel are essential for the normal defecation. According to the severity of intestinal dysfunction and SCI, we develop a set of nursing intervention based on the quantitative evaluation for the intestinal dysfunction patients after SCI, so as to make nursing more efficient and targeted. Nevertheless, insufficient research design and small size of sample are the limitations of this experiment. The effectiveness of nursing intervention based on quantitative evaluation needs further study.

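### Severity is graded only within study-group nursing, so as written there is no comparable baseline grade in the control group and the analysis gains no precision from it

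*Protocol article*

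**What the plan says.** All references are to the protocol article.

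- **Nursing in both groups (2.1).** The list introduced by "Nursing in study group involves" opens with a quantitative evaluation: "on the basis of the imaging examination results and clinical symptoms, the patients are scored in severe, moderate and mild". No cut-offs are given. The control paragraph begins "In control group, the patients are given the routine nursing, containing psychological nursing and the education of disease health" and continues with dietary advice. It mentions no grading.
- **Materials and methods (2).** On entry: "Fifty neurogenic bowel dysfunction patients after SCI confirmed via the imaging are included in this study". On allocation: "all the patients involved in the experiment are assigned a random number in a random envelope", and then "The patients are randomly divided into control group (25 cases) and study group (25 cases"). No stratification factor is named.
- **Statistical analysis (2.3).** Continuous variables go to independent t-tests and categorical variables to chi-square tests, at P below .05. No covariate is mentioned.
- **Result (3), Table 1.** The shell has rows for bowel function and for the SF-36 domains, and none for severity.
- **Discussion (4).** "According to the severity of intestinal dysfunction and SCI, we develop a set of nursing intervention based on the quantitative evaluation".

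**The concern.** The grade summarises how badly a patient is affected at the start, and the first-named primary outcome is recovery of bowel function. The plan also builds its intervention on severity. That makes the grade a plausible prognostic variable, and one that a 50-patient trial would want in its analysis.

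The text places it inside the experimental package. Followed literally, 25 patients receive a grade after allocation, as part of their nursing, and 25 receive none. The two groups could then not be compared on severity, and the grade could not serve as a covariate, because it would be missing for a whole arm. A grade reconstructed later for controls only, from records, would not be like-for-like with one assigned by the nursing team in the study group.

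At stake are sensitivity and interpretability. The trial is small, so any baseline variable that explains outcome variance is worth having. A reader of the results would also be unable to tell whether one group happened to start with more severe patients.

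**Working it through.** The article states no power, effect size, SD or severity distribution, so there is no figure of its own to reproduce. The placement of the grade is a matter of reading; the two calculations illustrate what it could cost.

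**1. Where the grade sits**

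| Element | Study group | Control group |
|---|---|---|
| Imaging at entry | yes (entry condition) | yes (entry condition) |
| Severity grade | yes, first item of nursing | not described |
| Use in allocation | none named | none named |
| Use in the planned tests | none | none |

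The inputs exist in both columns; the grade is described in only one.

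**2. Chance imbalance in severity**

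Inputs: N = 50, split 25:25 (Materials and methods). Assumption: K of the 50 patients are severe, K unknown.

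Let X be the number of severe patients in the study group. With unstratified allocation to fixed group sizes, X follows a hypergeometric distribution (50, K, 25). The difference in severe share is |X − (K − X)|/25 = |2X − K|/25. A gap of at least 20 points needs |2X − K| ≥ 0.20 × 25 = 5 patients.

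| K severe of 50 | Smallest qualifying gap (patients) | Probability |
|---|---|---|
| 10 | 6 | 7.4% |
| 16 | 6 | 12.8% |
| 17 | 5 | 23.2% |
| 20 | 6 | 14.8% |
| 24 | 6 | 15.6% |
| 25 | 5 | 25.8% |

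2X − K has the same parity as K, so a gap of exactly 5 patients is possible only when K is odd. That is why one patient more or less (24 against 25, 16 against 17) moves the answer by about 10 points. The fair summary is the range, about 7% to 26%.

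**3. Precision gained by adjusting**

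Inputs: n = 25 per group; alpha 0.05, two-sided (sidedness is not stated, so this is assumed). Assumptions: a continuous outcome, a true difference of 0.5 SD, and a grade that explains a share R² of outcome variance.

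Adjustment reduces the residual SD by the factor √(1 − R²), so the effective standardised difference is 0.5/√(1 − R²) and the noncentrality is that value × √(25/2). Power comes from the noncentral t distribution. Using 48 error degrees of freedom, or 46 to allow for a three-level grade, gives the same rounded results.

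| R² | 0.5/√(1 − R²) | Noncentrality | Power |
|---|---|---|---|
| 0 (unadjusted) | 0.500 | 1.768 | 41% |
| 0.10 | 0.527 | 1.863 | 45% |
| 0.25 | 0.577 | 2.041 | 52% |
| 0.40 | 0.645 | 2.282 | 61% |

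The gain is 4 to 20 percentage points over this range of R².

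**The case against.** The strongest case against has four parts.

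- **Randomisation already covers chance imbalance.** An unstratified, unadjusted randomised comparison is valid, and its 5% error rate allows for imbalance in severity. This stands in full. A reader might infer that the result would be biased; the documents do not support that.
- **The grade is recoverable.** A rater blind to group could grade everyone from baseline records. This stands too, so it would be wrong to say that severity cannot be used. It does not rescue the plan as written, which provides for no such grading, but it shows how cheap the remedy is.
- **A condensed article may leave baseline tables, strata and covariates to a fuller document, and it never says that controls go ungraded.** Partly right. Table 1 is an outcome shell, so its lack of a severity row proves little. But the article does state where the grading sits and which tests will be used, and the point rests on those two statements.
- **Severity is not shown to be prognostic.** A reader might infer that it is the main prognostic factor. The documents say only that the intervention was developed according to it. Plausible is as far as the text goes.

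A further tempting reading concerns the exclusion "patients who are unwilling to cooperate with the evaluation will be excluded". One could infer that it removes patients from the study group alone. The article gives it as an eligibility criterion, ahead of the allocation sentence, and does not define the evaluation meant. Nothing there indicates one-sided exclusion after randomisation.

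**Conclusion.** The point holds in a limited form. The article describes severity grading only as a component of study-group nursing, after allocation, and plans tests that do not use it. As written there is no comparable baseline grade in the control group. The consequence is lost precision and lost sight of chance imbalance; the validity of the comparison is not in question.

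The size depends on quantities that the documents do not give. The 7% to 26% chance of a 20-point gap rests on assumed numbers of severe patients from 10 to 25 of 50. The power figures rest on an assumed 0.5 SD effect, a continuous outcome and assumed R² values; if the grade explains little variance, the gain is small. How far a given imbalance would move the estimate cannot be stated without an assumed prognostic effect, for which the documents give no basis.

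This should be changed because the improvement is cheap and best made before allocation. The trial is not invalid without it.

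**What to change.** 1. Write down the criteria that separate mild, moderate and severe.
2. Grade all 50 patients by those criteria, from imaging and clinical symptoms, before the envelope is opened.
3. Report the grade by group as a baseline characteristic.
4. Include the grade as a covariate in the primary analysis: ANCOVA for continuous outcomes and logistic regression for binary ones, in place of the unadjusted t-test and chi-square test.
5. Optionally, stratify the envelopes by grade. With adjustment in place this is a refinement.

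The cost is grading 25 further patients from data that should already exist, agreeing the criteria, and slightly more analysis work. No patient procedure is added and the nursing in either group does not change.

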### Outcome

2.2

The primary outcomes are bowel function recovery and satisfaction of the patients. The secondary outcomes are quality of life evaluated by SF-36 questionnaire.^[12]^ The questionnaire involves physical pain, role physiology, physiological functions, social functions, vitality, general health, mental health, and role-motional.

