### Statistical analysis

2.3

The analysis of all data are carried out with the IBM SPSS Statistical software Windows version 20 (IBM Corp., Armonk, NY). Afterwards, all the data are described with appropriate characteristics such as mean, median, standard deviation as well as percentage. Continuous and categorical variables are analyzed using the independent *t*-tests and *χ*2-tests. For the significance level, the value of *P* needed to be less than .05.

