## Result

3

Comparison of clinical parameters between the 2 groups will be shown in Table 1.

**Table 1 T1:** Comparison of clinical parameters between the 2 groups.

Study group (n = 25)	Control group (n = 25)	*P* value
Bowel function		
Abdominal distension		
Constipation		
Defecation time		
Fecal incontinence		
Quality of life		
Physical functioning		
Role-physical		
Bodily pain		
General health		
Vitality		
Social functioning		
Role-motional		
Mental health		

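### Two unranked primary outcomes share one P<.05 threshold, so the overall false-positive risk exceeds 5% if any single significant primary result counts as success

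*Protocol article*

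**What the plan says.** The Outcome section (2.2), like the abstract, names two primary outcomes: "The primary outcomes are bowel function recovery and satisfaction of the patients". They are neither ranked nor combined. The SF-36 quality-of-life domains are explicitly secondary.

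The Statistical analysis section (2.3) covers all comparisons together. One sentence, beginning "Continuous and categorical variables are analyzed using the independent", assigns t-tests and chi-square tests by variable type. The next says that the P value "needed to be less than .05". Sidedness is not stated.

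No score or responder definition is given for bowel function recovery. The Result section says "Comparison of clinical parameters between the 2 groups will be shown in Table 1". In that table shell, bowel function is a heading over four rows: "Abdominal distension", "Constipation", "Defecation time" and "Fecal incontinence". The table has a P value column. Satisfaction, although primary, has no row.

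**The concern.** With two primary outcomes and no rule joining them, the plan does not say which result decides the trial. A reader of the final report could take any one significant primary result as the positive finding. Under that reading the 5% level holds for each test but not for the trial's main claim.

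The risk is larger if bowel function is analysed item by item, as the table layout suggests. Four bowel items plus satisfaction make five chances of a significant result. The plan also does not say what may be concluded if one bowel item improves and another does not.

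**Working it through.** **No figure to reproduce.** The article gives 25 patients per arm and P<.05, but no overall error rate, effect size or power. One test at .05 gives 5% by definition.

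**Inputs from the article**
- Primary outcomes named: 2 (Outcome).
- Bowel items listed: 4 (Table 1 shell).
- Level per test: .05 (Statistical analysis).
- Patients: 25 per arm (Materials and methods).

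**Assumptions, not in the article**
- Tests are two-sided, and errors in either direction count.
- Any one significant primary result counts as success.
- The bowel items are tested separately, and satisfaction is tested too (for the five-test case).
- Test statistics are approximately normal with a common pairwise correlation ρ, varied from 0 to 0.9.

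**Independent tests.** Family-wise error = 1 − 0.95^k.
- k = 2: 1 − 0.95² = 9.8%
- k = 4: 1 − 0.95⁴ = 18.5%
- k = 5: 1 − 0.95⁵ = 22.6%

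For five tests the upper bound under any correlation is 5 × .05 = 25%.

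**Correlated tests.** Simulation of 1,000,000 equicorrelated normal vectors, counting any |z| above the two-sided 5% critical value:

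| Tests | ρ = 0 | ρ = 0.5 | ρ = 0.7 | ρ = 0.8 | ρ = 0.9 |
|---|---|---|---|---|---|
| 2 (each named outcome as one measure) | 9.8% | 9.0% | 8.3% | 7.8% | 7.1% |
| 4 (bowel items only) | 18.5% | 15.6% | 13.0% | 11.4% | 9.3% |
| 5 (bowel items plus satisfaction) | 22.6% | 18.3% | 14.9% | 12.7% | 10.2% |

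**Variations**
- Four bowel items correlated at 0.3, 0.5 or 0.7, with satisfaction independent: 21.5%, 19.8%, 17.4%.
- Only false positives favouring the study group, five tests: 11.8% at ρ = 0 and 9.1% at ρ = 0.5, against 2.5% for one test in that direction.
- Binary items at 25 per arm, exact size of one nominal 5% chi-square test for event rates of 0.1 to 0.8: about 4.9-6.5% uncorrected, about 0.6-3.3% with continuity correction. Correction would therefore pull the totals down. The article does not say which items are binary or whether a correction applies.
- If all primary tests had to be significant, the error would be at most 5%. No such rule is stated.

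**The case against.** The strongest objection is that much of this is inference. No sentence says that the four bowel items are tested separately. That is read from an empty table shell in which no cell shows which rows will carry a P value. Satisfaction has no row at all. A condensed article may also leave hierarchy and multiplicity to a fuller protocol or analysis plan, and its Discussion already concedes weak design and small size. The first part stands: four or five separate tests must be labelled as a reading. The second stands only in part, because the article does more than stay silent. It fixes plural primaries and a flat threshold, and even the narrowest count of two tests gives more than 5% if either may win.

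Three stronger readings are tempting but not supported:
- **That the false-positive risk simply is 15-23%.** This range needs five tests, an any-one-wins rule, two-sided errors and a correlation between 0 and 0.7. The article states none of these.
- **That all 13 comparisons (five primary plus eight SF-36 domains) bear on the primary claim.** SF-36 is explicitly secondary and sits under its own table heading, so it cannot establish bowel recovery. Satisfaction, listed separately, cannot either.
- **That the intervention may relieve constipation while worsening incontinence.** The study-group programme also includes anal contraction exercises, and nothing in the article suggests worsening. The sound point is only that no rule covers items that disagree.

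**Conclusion.** The point holds in conditional form. The article names two unranked primary outcomes and one P<.05 threshold, with no rule for combining or adjusting them. If any one significant primary result is read as success, the overall two-sided error exceeds 5% in every case in the table under the normal approximation. It is about twice nominal on the narrowest count (two tests, low to moderate correlation) and three to four and a half times nominal for five tests at correlations of 0.7 down to 0. Even at correlations of 0.8-0.9, five tests give 10-13%.

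The size depends on the assumed correlations and on inferred separate testing, and continuity-corrected tests on binary items would reduce it. What does not depend on them is that the article fixes no single result, or combination of results, that decides the primary question.

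**What to change.** **Preferred.** Before data are seen, name one primary bowel-function variable or score and test it at two-sided 5%. Make satisfaction and the other bowel items secondary. The change is one of wording and costs nothing in alpha.

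**Alternative.** Keep the listed primary tests, state how many there are, and apply Holm across all of them. Limit the conclusion to the specific items that stay significant after adjustment. Claim bowel function recovery only under a pre-stated rule for which item or items must succeed. Holm alone does not settle this, since one adjusted-significant item among four still leaves open whether function has recovered.

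In either case, report the SF-36 domains as supportive.

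**Cost of the alternative.** The first Holm step is stricter: .05/2 = .025 for two tests, .05/5 = .01 for five. For a continuous outcome analysed by two-sided t-test with 25 per arm and 80% power, the detectable difference rises from about 0.81 SD at .05 to 0.90 SD at .025 or 1.00 SD at .01. These figures do not carry over to binary items.
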